## Methods

### Research Design

This study will use a cluster-randomized control trial design. A conceptual model is provided in Figure 1. The intervention protocol will be pre-registered before data collection in ClinicalTrials.gov (ref: NCT05027880), and strictly follow the CONSORT (Consolidated Standards of Reporting Trials) guidelines [18,19]. At least 3 classes in the same grade of the participating school will be randomized (using computer-generated random numbers) into the (1) SIGMA group, (2) SSI-GP group, and (3) ST group (active control condition group), which will provide ST intervention at the same time. All participants will receive regular interventions in school. Three repeated assessments of the measures will be conducted for the 3 groups simultaneously at (1) baseline, (2) 2-week postintervention, and (3) 8-week postintervention (Figure 2). The cluster randomization at the classroom level can balance the risk of contamination between the intervention and active control groups and the school heterogeneity due to the school culture, schedule, and management.

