### Implementation Content

#### SIGMA

The SIGMA intervention group will adapt the SSI-GP protocol in two ways: (1) by introducing the growth mindset of emotions rather than personality and (2) by providing an experiential process of negative emotion change. SIGMA also consists of five components: (1) an introduction to emotions and the brain for conveying a scientific understanding of emotion and growth mindset of negative emotions; (2) stories and testimonials from high school–aged youths who described their beliefs that people’s negative emotion states (eg, anxiety, depression, and stress) are malleable, and how these mindsets influence their coping with anxiety; (3) emotion changing experience induced by short videos; (4) common questions and misconceptions about growth mindset; and (5) self-persuasion writing exercises in which the participants write notes to younger students about the growth mindset of emotion. Table 1 presents the key elements of the interventions. For participants at each school who belong to the SIGMA group, we will randomly select half of them to give them booster messages with core intervention content every 2 weeks between the 2-week posttest and the 2-month follow-up survey, that is, a total of 5 weekly booster messages will be sent to half of the participants of the intervention group, which will help us determine the most effective way of implementing the intervention.

**Table 1 table1:** Intervention elements.

Intervention elements	SIGMA^a^ (45 minutes)	SSI-GP^b^ (45 minutes)	ST^c^ (45 minutes)
Science knowledge about neural plasticity of the brain	✓ Growth mindset of negative emotions	✓ Growth mindset of personality	Nil Science videos about emotions
Stories and testimonials from high school-aged youths	✓ Focused on emotion changing experience	✓ Focused on personality change	✓ Focused on emotion sharing
Experiential exercises	✓ Emotion coping strategies	Nil	Nil
Self-persuasion writing exercises	✓ Focused on the malleability of negative emotion	✓ Focused on the malleability of personality	✓ Focused on sharing emotion to close others

^a^SIGMA: single-session intervention of growth mindset on negative emotions.

^b^SSI-GP: single-session intervention growth mindset of personality.

^c^ST: support therapy.

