### Data Analysis

An intention-to-treat analysis will be conducted for any missing data. Two-level analyses will be used to account for cluster randomization [37]. To examine the effects of the interventions, multilevel regression will be used to test the group effect, time effect, and their interaction effect on outcome measures. Additionally, we will calculate effect sizes using estimated marginal means; these effect sizes compare mean gain scores (Cohen *d*), reflecting changes in each outcome from baseline to 2 follow-ups for youths receiving the mindset versus active control interventions. The effect sizes will also be compared between participants in the intervention group who receive booster messages and those who do not. A *P* value of <.05 will be considered statistically significant, and SPSS version 26 (IBM Corp) will be used for all statistical analyses.

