## Discussion

### Overview

We anticipate that SIGMA, which highlights that emotion states are changeable, will significantly enhance the growth mindset of emotion and reduce general anxiety symptoms and secondary outcomes compared to SSI-GP and the active control. However, the effect size will be small because single-session self-help interventions are low-dosage interventions. SSI-GP is hypothesized to have better outcomes than the active control group. The half with booster messages in the SIGMA group will have better outcomes than the half without boosters, especially in the 8-week follow-up.

To date, this will be one of the few randomized controlled trials to apply a single-session growth mindset intervention to reduce anxiety. As focusing on the key aspects and using effective ways to make changes are the key mechanism of effective SSI, addressing the key aspects that can secure changes is essential for designing SSIs. This 3-arm randomized controlled trial will help elucidate the mechanisms of change in adolescent anxiety symptoms: believing that negative emotion can change (SIGMA), believing that personality can change (SSI-GP), or receiving support (active control). This proposed study will find the potent core element of brief intervention in helping youth with anxiety.

This study will also be a pioneer study examining the self-administered web-based intervention among Chinese adolescents. There is a paucity of research in the Chinese context on effective implementation strategies for self-administrative SSI. As the effect size of SSI varies from small to medium in extant interventions, the dedicated design and careful implementation matter in the efficacy of the study. This study will provide a clear protocol of implementation content and strategies, which will be helpful for the future use and development of SSIs.

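### The booster comparison uses gains from baseline to both follow-ups, but boosters start after week 2: the 2-week part is uninformative and the 8-week part, though unbiased, loses precision

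*Protocol article*

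**What the plan says.** In the protocol article, the SIGMA section under Implementation Content describes a second randomised step inside the SIGMA arm. At each school, "we will randomly select half of them to give them booster messages with core intervention content", and these go out "between the 2-week posttest and the 2-month follow-up survey". Research Design places the assessments at baseline, 2 weeks and 8 weeks after the intervention, so the 2-week survey is the last measurement before any booster.

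Data Analysis defines the effect sizes as mean gain scores, "reflecting changes in each outcome from baseline to 2 follow-ups for youths receiving the mindset versus active control interventions". The next sentence carries them over to the booster question: "The effect sizes will also be compared between participants in the intervention group who receive booster messages and those who do not". It names no other starting value or time point.

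The Overview of the Discussion states the expectation: "The half with booster messages in the SIGMA group will have better outcomes than the half without boosters, especially in the 8-week follow-up".

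The SIGMA section also gives the booster frequency in two ways that do not agree (once every two weeks, and as five weekly messages). Those statements must be reconciled, but under either one the boosters follow the 2-week survey, so this point is unaffected.

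**The concern.** The booster question is what the messages add to the session by week 8. The stated metric does not fit that question in two ways.

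- The gain from baseline to week 2 is complete before the first booster. Comparing it between the halves can show only chance, yet the stated metric includes it, and the word *especially* in the Discussion implies some benefit at that visit too.
- The gain from baseline to week 8 includes all the change before the boosters. The 2-week score, which could remove much of the variation between students, is collected but plays no part in this comparison.

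The SIGMA section says the comparison will help to decide how best to implement the intervention, and Aims and Objectives makes the most effective implementation strategy the overarching goal. The comparison splits one arm in two, so it has half the group size of the main contrasts and can least afford to lose precision.

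**Working it through.** **Inputs from the article (Sample Size Determination).** d = 0.33, power 0.80, alpha .05, 146 completers per arm, 183 recruited per arm. The article does not state whether the test is two-sided; two-sided is used here because it reproduces the figure.

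**The plan's own figure.** n per arm = 2(1.96 + 0.84)²/0.33², which rounds up to 145; the t-test version gives 145.1, hence 146. Then 146/0.8 = 182.5, so 183 per arm and 549 in total. The sample size reproduces. The article gives no figure for the booster comparison.

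**Size of the halves.** 146/2 = 73 completers each.

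**Assumed inputs.** The article gives no correlations. Let r08 be the correlation of baseline with week 8 and r28 that of week 2 with week 8. The outcome SD is set to 1 at every visit and clustering is ignored.

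**Formulas.** Variance per student, v, is 2(1 − r08) for the gain from baseline, 1 − r08² for ANCOVA on baseline, and 1 − r28² for ANCOVA on week 2. The detectable d at 80% power is 2.80 × √(2v/73).

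| Analysis of the 8-week contrast | r08 = 0.5, r28 = 0.6 | r08 = 0.6, r28 = 0.7 |
|---|---|---|
| Gain from baseline | v = 1.00, d = 0.46 | v = 0.80, d = 0.41 |
| ANCOVA on baseline | v = 0.75, d = 0.40 | v = 0.64, d = 0.37 |
| ANCOVA on week 2 | v = 0.64, d = 0.37 | v = 0.51, d = 0.33 |

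**Splitting the saving.**

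- Gain to ANCOVA, both on baseline: 1 − 0.75/1.00 = 25%; 1 − 0.64/0.80 = 20%.
- Baseline to week 2, both as ANCOVA: 1 − 0.64/0.75 = 15%; 1 − 0.51/0.64 = 20%.
- Together: 1 − 0.64/1.00 = 36%; 1 − 0.51/0.80 = 36%.

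**Equal correlations.** If r08 = r28, the two ANCOVA variances are the same, so moving the starting value to week 2 saves nothing. Only the gain-to-ANCOVA step remains: 25% at 0.5, 20% at 0.6, and 1 − 0.51/0.60 = 15% at 0.7. Adjusting for both scores can still help: with all three correlations at 0.6, v falls from 0.64 with one covariate to 0.55 with two.

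**Sensitivity.** Over six assumed sets (r08 from 0.4 to 0.7, r28 from 0.6 to 0.8), the baseline-gain variance is 1.18 to 2.22 times that of ANCOVA on week 2. Power for a 0.33 SD booster effect is 44-73% with baseline gains and 70-91% with ANCOVA on week 2.

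**Bias.** In 10,000 simulated trials with 73 per half, a true booster effect of −0.20 SD, r08 = 0.5, r28 = 0.7 and a baseline-to-week-2 correlation of 0.6:

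| Contrast | Mean | Standard error |
|---|---|---|
| Gain, baseline to week 8 | −0.199 | 0.167 |
| ANCOVA of week 8 on week 2 | −0.199 | 0.119 |
| Gain, baseline to week 2 | 0.00 | 0.150 |

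Both 8-week estimates centre on the true effect. The 2-week contrast centres on zero, as the timing requires.

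**The case against.** The strongest reply is that the planned 8-week estimate is not wrong. The booster half is chosen at random, baseline is a valid measurement before the boosters, and the simulation confirms that there is no bias. This stands. A reader might infer that baseline is an incorrect starting value, or that a chance gap at week 2 would pass into the result as a spurious booster benefit or harm. The documents do not support that. With 73 per half, raw week-2 differences have a standard error of √(2/73) = 0.166 SD, so gaps up to about 0.33 SD are ordinary; but variation of this kind is already covered by the standard error and P value of the 8-week contrast.

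Second, the article nowhere says that a 2-week difference will be reported as a booster effect. The gain definition is written for mindset against active control, the booster sentence only inherits it, and the Discussion wording is loose and points mainly to week 8. This stands in part: the inherited definition covers both follow-ups, no other is offered, and the stated expectation is not confined to week 8.

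Third, the 36% saving combines two changes, and the larger share, or half of it, comes from dropping gain scores and not from the choice of starting value. This stands, and the working separates the two.

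Fourth, the booster contrast is in none of the three hypotheses, the sample size is not built on it, and covariates are commonly left to an analysis plan. The first two parts are true and limit the weight of the point. The last does not dispose of it, because the article does state a metric, and that metric does not match the booster's timing.

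**Conclusion.** The point holds as a mismatch in timing and a loss of precision, not as bias. The baseline-to-2-week contrast between the booster halves has a true value of zero, and the Discussion should not allow for a booster effect there. The baseline-to-8-week gain contrast is valid but less precise than it could be with data already collected.

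Under the assumed correlations (0.5 to 0.6 and 0.6 to 0.7), with 73 per half and clustering ignored, the variance could fall by about 36% and the detectable d from 0.41-0.46 to 0.33-0.37. It would be too strong to credit all of this to the starting value: 20 to 25% comes from replacing gains by ANCOVA, and 15 to 20% of what remains from using week 2. Were the two correlations equal, the second part would vanish. This is a low-cost improvement to a supporting comparison; it casts no doubt on the main three-arm analysis.

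**What to change.** Replace the booster sentence in Data Analysis with wording such as: *Within the SIGMA arm, the booster effect is the difference between boosted and unboosted students in the 8-week score, adjusted for the 2-week (pre-booster) and baseline scores, with class (or school) as a factor. The 2-week difference between the halves describes balance before the boosters and is not interpreted as a booster effect.*

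Amend the Overview of the Discussion so that a booster benefit is expected at 8 weeks only.

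The cost is two small edits. No new data, visits or participants are needed.

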### Ethics Approval

The study has obtained research ethics approval from the institutional review board of the principal investigator’s university (HSEARS20201004001-01). This trial was preregistered at ClinicalTrials.gov (NCT05027880). Participation will be voluntary. Informed written consent or digital consent will be obtained from parents and participants. We will remind the participants that they have the right to terminate the intervention or omit any questionnaire questions and assure the confidentiality of their answers. We will also provide additional information for referral services to the student participants. Students are also invited to indicate if they need further support from school social workers or counselors in the postintervention questionnaire. With the participant’s assent, we will refer the participant to the school caring professionals. All identifiable information will be removed, and codes will replace names to ensure privacy. All personally identifiable data will be locked up and destroyed 3 years after the study ends. Participants’ data will not be identifiable in any publication or reporting.

## Results

Recruitment will start in December 2022, and data collection is expected to end in 2023. Results are expected to be available in January 2024. We also intend to make the publications available in 2024. The findings of this trial will be presented as well at conferences. We will only report aggregated group data, and no personal information will be leaked.

## Discussion

### Overview

We anticipate that SIGMA, which highlights that emotion states are changeable, will significantly enhance the growth mindset of emotion and reduce general anxiety symptoms and secondary outcomes compared to SSI-GP and the active control. However, the effect size will be small because single-session self-help interventions are low-dosage interventions. SSI-GP is hypothesized to have better outcomes than the active control group. The half with booster messages in the SIGMA group will have better outcomes than the half without boosters, especially in the 8-week follow-up.

To date, this will be one of the few randomized controlled trials to apply a single-session growth mindset intervention to reduce anxiety. As focusing on the key aspects and using effective ways to make changes are the key mechanism of effective SSI, addressing the key aspects that can secure changes is essential for designing SSIs. This 3-arm randomized controlled trial will help elucidate the mechanisms of change in adolescent anxiety symptoms: believing that negative emotion can change (SIGMA), believing that personality can change (SSI-GP), or receiving support (active control). This proposed study will find the potent core element of brief intervention in helping youth with anxiety.

This study will also be a pioneer study examining the self-administered web-based intervention among Chinese adolescents. There is a paucity of research in the Chinese context on effective implementation strategies for self-administrative SSI. As the effect size of SSI varies from small to medium in extant interventions, the dedicated design and careful implementation matter in the efficacy of the study. This study will provide a clear protocol of implementation content and strategies, which will be helpful for the future use and development of SSIs.

This project has theoretical, practical, and clinical contributions. Examining the efficacy of the notion of malleability of negative emotion on youth anxiety will advance the understanding of the impact of implicit theory and mental health symptoms. The easy-access self-help program will enable adolescents with anxiety symptoms to access timely help, and reduce the risk of deterioration of anxiety symptoms and development of comorbid mental health problems before adolescents can access therapy provided by a trained therapist or psychiatrist. If proven effective, SIGMA will benefit a proportion of youths who would otherwise go without service entirely. It can also benefit youth on the waitlist for psychiatric services by invoking intrinsic motivation and avoiding hesitance to get treatment. It can also serve as a complement to multisession psychosocial treatments. This project may provide a generalizable model for the development and implementation of SSI among youth people in the Chinese context.

### Limitations

There are limitations that need to be considered. First, as this study does not exclude individuals based on the severity of their anxiety symptoms, the efficacy of the interventions to reduce anxiety symptoms of students without anxiety or with low levels of anxiety may not be significant and thus affects the statistical significance on the whole. However, the proposed intervention can be inclusive to youths with a diverse range of anxiety problems and offers a unique opportunity to study the differentiated impacts with subgroup analyses. We expect the secondary outcomes will have significant changes after the intervention, even for those with low-level anxiety symptoms. Second, there is no waitlist control group as all 3 groups are implemented with specific interventions, with even the control group receiving ST (active control). In this study, we aim to compare the effects of different interventions with specific strategies. However, the setting of a waitlist control group will help in better understanding the effect of interventions overall.

### Conclusions

This study presents the evidence-based implementation of web-based single-session growth mindset interventions for student anxiety and compares the efficacy of SSIs using growth mindsets on negative emotions and growth mindsets on personality. Our study will provide an example of the implementation of SSIs among the Chinese adolescents and will help to develop easy-access, low-cost, and scalable interventions for mental health promotion among young people.

## Abbreviations

CONSORT: Consolidated Standards of Reporting Trials
GAD-7: Generalized Anxiety Disorder-7
SIGMA: single-session intervention of growth mindset on negative emotions
SSI: single-session intervention
SSI-GP: single-session intervention of growth mindset of personality
ST: support therapy
TFA: theoretical framework of acceptability
WEMWBS: Warwick-Edinburgh Mental Well-being Scale
